### Participants

2.2

#### Definition of dyslipidemia and metabolic syndrome

2.2.1

Dyslipidemia is defined according to the 2022 Korean Society of Lipid and Atherosclerosis (KSoLA) guidelines as the presence of any one or more of the following: LDL-C ≥160 mg/dL, TC ≥240 mg/dL, HDL-C <40 mg/dL, or TG ≥200 mg/dL (9). Metabolic syndrome is defined according to the modified NCEP-ATP III criteria for the Asian population as the presence of three or more of the following five components: (1) abdominal obesity (waist circumference ≥90 cm for men or ≥85 cm for women, based on Korean cutoffs); (2) elevated triglycerides (≥150 mg/dL or on lipid-lowering therapy for hypertriglyceridemia); (3) reduced HDL-C (<40 mg/dL for men, <50 mg/dL for women); (4) elevated blood pressure (systolic ≥130 mmHg or diastolic ≥85 mmHg, or on antihypertensive therapy); and (5) elevated fasting glucose (≥100 mg/dL or on antidiabetic therapy).

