**Figure 1 f1:**
[figure not shown]
The flowchart of the study.

**Table 1 T1:** Participant timeline: schedule of enrollment and assessments.

Visit	Visit 1 (Baseline)	Visit 2	Visit 3 (EOS)	UV
Day (Week)	**D1 (W0)**	**D169 (W24)**	**D337 (W48)**	**-**
Visit window	**-**	**-2M~+1M**	**-2M~+1M**	**-**
Written informed consent¹)	●			
Demographic information²)	●			
Baseline disease information³)	●			
Cardiovascular risk classification	●			
Medical history^4^)	●			
Prior/concomitant medication^5^)	●	●	●	○
Physical examination	●	●	●	○
Vital signs (blood pressure, pulse rate, body temperature)	●	●	●	○
Physical measurement^6^)	●	○	●	○
Serum lipids^7^)	●	●	●	○
Blood glucose and glucose metabolism parameters^8^)	○	○	○	○
Cardiovascular risk biomarker (hs-CRP)^9^)	○	○	○	○
Blood chemistry (AST, ALT, CK)¹^0^)	●	●	●	○
Apolipoprotein B (ApoB)¹¹)	○	○	○	○
TLC education and checking	●	●	●	○
Inclusion and exclusion criteria checking	●			
Participant enrollment	●			
IP prescription/administration checking	●	●	●	○
Medication adherence & persistence¹²)		●	●	○
AEs¹³)		●	●	○

AEs, Adverse events; EOS, end of study; TLC, Therapeutic Lifestyle Change; UV, unscheduled visit.

**●** To be conducted in all participants enrolled in the study.

**○** Optional items for which information will be collected only if test results are obtained in routine clinical practice. Information will not be collected if there are no test results.

^1)^All study related procedures should be performed after written informed consent is obtained; After informed consent is obtained, a participant identifier will be assigned.

^2)^Date of birth, age, sex, pregnancy/breastfeeding, and smoking history will be collected.

^3)^Date of initial diagnosis of dyslipidemia/metabolic syndrome, presence of pre-diabetes/diabetes, date of initial diagnosis of diabetes, family history of premature coronary artery disease, presence of hypertension, and presence of target organ damage will be collected. If classification of cardiovascular disease risk groups has been previously performed, or if the necessary information for classifying cardiovascular disease risk groups is available, allowing the investigator to classify the risk groups directly, the relevant information will be collected. Cardiovascular risk classification (per **Table 2**) will be assigned at Visit 1 by the treating investigator (Section 2.3) and will not be re-assigned during follow-up.

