^4)^Medical history (including surgical/procedure history) within 12 weeks prior to Visit 1 will be collected. For medical history relevant to the inclusion and exclusion criteria, information throughout lifetime will be collected, unless otherwise specified.

^5^Medication information on lipid regulators, antidiabetics, and other drugs will be collected. Drugs administered within 4 weeks prior to Visit 1 will be collected as prior medication. If there is a history of treatment with lipid regulators within the predefined duration of information collection for prior medication, medication information on lipid regulators within 8 weeks prior to Visit 1 will be collected. In addition, if results of prior serum lipid or blood glucose and glucose metabolism parameter tests are used as baseline (Visit 1) results, information on lipid regulators will be collected in the same manner as described above based on the time point of the tests. Drugs administered from after the first study drug dosing to the end of observation will be collected as concomitant medication.

^6)^Height, weight and waist circumference will be measured, and body mass index (BMI) will be calculated. Height will be measured at Visit 1 only.

^7)^LDL-C, TC, TG, HDL-C, and non-HDL-C will be tested. LDL-C may be measured either directly (by homogeneous direct assay) or calculated using the Friedewald formula; when TG ≥400 mg/dL, direct LDL-C measurement is required (Section 2.7). If test results obtained within 4 weeks prior to Visit 1 are available and the participant had no treatment with lipid regulators within 4 weeks prior to the test or was treated with lipid regulators using the same dosage and administration for at least 8 weeks, the test results may be used as baseline (Visit 1) results. Before testing, a blood sample is to be collected after at least 12 hours of fasting, if possible; If it is difficult for the participant to remain fasted for 12 hours, at least 9 hours of fasting should be maintained.

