#### Inclusion criteria

2.2.2

To be eligible for this study, participants must meet all of the following criteria.

Age ≥19 years old at the time of written informed consent.Participants diagnosed with dyslipidemia and metabolic syndrome as defined in Section 2.2.1.Participants who had no treatment history with lipid regulators within 4 weeks prior to Visit 1 or who had insufficient therapeutic effects from ≥8 weeks of treatment with lipid regulators using the same dosage and administration (these two subgroups—treatment-naïve and inadequate-response—will be pre-specified and analyzed separately as a key subgroup analysis, as they may exhibit differential LDL-C response).Participants who meet the following LDL-C levels according to the classification of cardiovascular disease risk groups (9) (**Table 2**) at Visit 1 or who are planned to be treated with LivaloZet^®^ Tablets based on the judgment of the investigator.Participants who voluntarily sign the informed consent form for study participation.

**Table 2 T2:** Classification of cardiovascular risk groups and target LDL-C level.

Risk group	Criteria for classification	LDL-C (mg/dL)
Very high risk group	Coronary artery disease	≥ 55
High risk group	Atherosclerotic ischemic stroke, transient ischemic attack, carotid artery disease, peripheral arterial disease, abdominal aortic aneurysm, diabetes mellitus (duration of disease ≥10 years; or concurrent major cardiovascular disease risk factors† or target organ damage‡)	≥ 70
Diabetes group	Diabetes mellitus (duration of disease <10 years, no major cardiovascular disease risk factors†)	≥ 100
Moderate risk group	≥2 major cardiovascular disease risk factors†	≥ 130
Low risk group	≤1 major cardiovascular disease risk factor†	≥ 160

† Major cardiovascular disease risk factors (1): Age: ≥ 45 years old in men, ≥ 55 years old in women; (2) Family history of early onset coronary artery disease: Parents or siblings who had an onset of coronary artery disease at the age of <55 years in men and <65 years in women; (3) Hypertension: Systolic blood pressure (SBP) ≥ 140 mmHg or diastolic blood pressure (DBP) ≥ 90 mmHg or treatment with antihypertensives; (4) Current smoking; (5) High density lipoprotein-cholesterol (HDL-C) < 40 mg/dL (If HDL-C ≥ 60 mg/dL, 1 will be subtracted from the number of major risk factors).

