#### Secondary endpoints

2.4.2

Percent change from baseline in LDL-C level at Week 48.Absolute change from baseline in LDL-C level at Week 24 and Week 48.Percent change and absolute change from baseline in lipid parameters at Week 24 and Week 48: Total cholesterol (TC), triglyceride (TG), HDL-C, non-HDL-C. Apolipoprotein B (Apo B) is not a required measurement; it will be collected and analyzed descriptively only when available from routine clinical practice.Achievement rate (%) for target LDL-C level at Week 24 and Week 48: Very high risk group <55 mg/dL, high risk group <70 mg/dL, diabetes group <100 mg/dL, moderate risk group <130 mg/dL, and low risk group <160 mg/dL according to the classification of cardiovascular disease risk groups.Medication adherence (proportion of days covered, PDC), persistence (time from initiation to discontinuation), dose modifications, and treatment switching during the 48-week observation period.

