#### Subgroup analyses

2.6.3

Pre-specified subgroup analyses will be performed for the primary endpoint by: (1) cardiovascular risk category; (2) prior lipid-lowering treatment history (treatment-naïve vs inadequate response); (3) dose (2/10 mg vs 4/10 mg); (4) age (<65 vs ≥65 years); (5) sex; (6) presence of diabetes mellitus; and (7) baseline LDL-C (<130 vs ≥130 mg/dL). Subgroup analyses are descriptive; no formal interaction testing is planned.

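### The baseline-LDL-C subgroup splits on the same single reading that is the denominator of the percent change, so regression to the mean builds in a larger fall at ≥130 mg/dL; other uncontrolled lipid changes may contain it too

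*Protocol article*

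**What the plan says.** **Entry.** Inclusion requires "Participants diagnosed with dyslipidemia and metabolic syndrome as defined in Section 2.2.1". Section 2.2.1 defines dyslipidemia as any one of "LDL-C ≥160 mg/dL, TC ≥240 mg/dL, HDL-C <40 mg/dL, or TG ≥200 mg/dL", with no sample date and no confirmatory test. Metabolic syndrome needs three of five components, two of which are TG and HDL-C cut-offs. A further criterion admits "Participants who meet the following LDL-C levels according to the classification of cardiovascular disease risk groups (9"), by the Table 2 values, "at Visit 1 or who are planned to be treated with LivaloZet^®^ Tablets based on the judgment of the investigator".

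**Baseline.** Table 1 schedules serum lipids at Visit 1. Under footnote 7, if a result from the preceding 4 weeks exists and lipid treatment was absent or stable, "the test results may be used as baseline (Visit 1) results". The article describes no averaging and no separate baseline draw.

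**Endpoints.** The primary endpoint is percent change in LDL-C at Week 24 (section 2.4.1). Section 2.4.2 adds "Percent change and absolute change from baseline in lipid parameters at Week 24 and Week 48", including TG and HDL-C. The study has a single arm.

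**Subgroup.** The last item of section 2.6.3 is "7) baseline LDL-C (<130 vs ≥130 mg/dL"). Subgroups are described as descriptive, without interaction tests.

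**Limitations.** The Discussion names the missing comparator, confounding by indication, selection bias, missing data, LOCF and inter-laboratory variability. It does not name regression to the mean.

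**The concern.** A single reading is the patient's usual level plus within-person variation. Patients grouped because one reading was high will, on average, read lower next time without any treatment effect; those grouped because it was low will read higher. A control arm would normally subtract this, and here there is none.

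In the baseline-LDL-C subgroup the mechanism does not depend on how patients were recruited. The reading that assigns the group is the denominator of the outcome. A high error in it pushes the patient into the ≥130 group and also enlarges the percent fall; a low error does the reverse. The table would suggest that the product works better at higher baseline LDL-C even if every patient had the same response.

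For the cohort-wide changes the same mechanism operates only where the qualifying result is also the baseline. None of the planned sensitivity analyses addresses it: observed cases, multiple imputation, MMRM and the per-protocol set deal with missing data and deviations, and the propensity score deals with dose choice.

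**Working it through.** **1. The plan's own precision figure (section 2.5).** SD 22%, n = 8,000: 1.96 × 22 / √8,000 = 0.48 points, which agrees with the stated ±0.5%.

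**2. Subgroup contrast, by formula.** The documents give neither a within-person variation nor an LDL-C distribution, so these are assumptions: single readings log-normal, median 135 mg/dL, total log-SD 0.27, within-person CV from 6% to 12%.

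On the log scale the expected drift of a second reading back to the mean is λ × (distance of the first reading from the mean), with λ = CV² / 0.27².

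- The cut lies at z = ln(130/135)/0.27 = −0.140.
- Mean z is +0.711 in the ≥130 group and −0.889 in the <130 group. The groups therefore differ by 1.600 × 0.27 = 0.432 log units at baseline.
- Spurious gap with no effect ≈ λ × 0.432. If everyone's true value falls by 50%, each percent change is computed on half the value and the gap halves.

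| CV | λ | Gap, no effect (points) | Gap, uniform 50% fall (points) |
|---|---|---|---|
| 6% | 0.0036/0.0729 = 0.049 | 2.1 | 1.1 |
| 8% | 0.0064/0.0729 = 0.088 | 3.8 | 1.9 |
| 10% | 0.0100/0.0729 = 0.137 | 5.9 | 3.0 |
| 12% | 0.0144/0.0729 = 0.198 | 8.5 | 4.3 |

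A simulation of 2,000,000 patients per row agrees. At CV 8% with a uniform 50% fall it gives −50.5% (≥130) against −48.6% (<130).

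A second simulation used other assumptions: usual LDL-C mean 120–140 mg/dL with SD 35, CV 6–12%, and entry by the section 2.2.1 rule. It gives a gap of 1.3 to 4.8 points with a uniform 50% fall and 2.6 to 9.6 with no effect. Together the two models span about 1 to 5 points.

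**3. Overall estimates, if the qualifying result is always the baseline.** Same second simulation, with usual TG median 130 mg/dL and log-SD 0.5, usual HDL-C mean 50 mg/dL and SD 12, CV 15–28% for TG and 5–9% for HDL-C.

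- LDL-C, all qualifiers, true 50% fall: mean change −50.10% to −50.44%, a bias of about 0.1 to 0.4 point. With no effect it is −0.2 to −0.9 point.
- TG, all qualifiers, no effect: −2.3 to −10.0 mg/dL on average.
- HDL-C, all qualifiers, no effect: +0.04 to +0.3 mg/dL.
- Only patients past the cut-off on that analyte, no effect: TG ≥200, −3.7 to −11.1%; HDL-C <40, +1.4 to +4.5%.

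**4. Does a correction from Week 24–48 variance work?** Take half the variance of the Week 24 to Week 48 log difference as CV², and add back λ × (log baseline − mean log baseline). In the model of step 2 with a uniform 50% fall, the corrected gap is 0.0 points when nothing but within-person variation separates the two visits. If true levels also shift between the visits with an SD of 10%, the variance is overstated and the correction overshoots by about 1.5 points.

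**The case against.** **The qualifying result need not be the baseline.** This stands. Patients must be diagnosed, and Table 1 footnote 3 collects "Date of initial diagnosis of dyslipidemia/metabolic syndrome", so the diagnosis may be old. Inadequate responders enter on stable treatment, and investigator judgment can replace the Visit 1 LDL-C threshold. Any one of four analytes suffices, so most patients need not be extreme on a given one. The cohort-wide changes may contain regression to the mean; the text does not establish that they do.

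**The primary result is barely touched.** This also stands. A reader might infer that the bias in the overall LDL-C change exceeds the ±0.5% precision. It does not: 0.1 to 0.4 point is below that, and small beside the 52–53% reduction cited in the Discussion. Larger LDL-C figures arise only in patients selected on LDL-C itself.

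**The TG effect is overstated.** A reader might infer that the reported TG fall would be largely artefact. The larger percentages hold only for patients past the TG cut-off, rest on assumed variation, and cannot be carried over to the cohort.

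**Interpretation is already restricted.** Subgroups are descriptive and causal claims are disclaimed. This helps only in part: without an interaction test, the two group means still stand side by side and their difference is still biased. The general caveat about the missing comparator does not warn of this mechanism.

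**Conclusion.** The point holds in limited form. The baseline-LDL-C subgroup is fixed badly: grouping value and denominator are the same single reading, which favours the ≥130 group by about 1 to 5 points under a uniform 50% fall. That is larger than the half-width quoted for the whole cohort. The direction follows from the design; the size rests on an assumed within-person CV of 6–12% and assumed LDL-C distributions.

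For the cohort-wide TG, HDL-C and LDL-C changes, regression to the mean is possible and unnamed. Its size depends on how often the qualifying sample is also the baseline, which the article does not say. The primary LDL-C estimate is not materially threatened.

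**What to change.** 1. Keep the raw baseline-LDL-C table and state in section 2.6.3 that its contrast is not to be read as a differential effect.
2. Report beside it a version corrected for regression to the mean, with within-person variance estimated from Week 24 to Week 48 in participants whose lipid therapy did not change.
3. Where both a pre-Visit 1 and a Visit 1 result exist on the same treatment, group on the earlier and use the later as baseline. Footnote 7 lets the earlier result stand in for Visit 1, so such pairs may be few.
4. Give the same corrected estimates for TG and HDL-C as supportive results.
5. Record whether the qualifying and baseline samples coincide.
6. Name regression to the mean in the limitations.

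TG and HDL-C changes should not be stratified by their own baseline cut-off, because that repeats the defect. With no effect, median TG 170 mg/dL, total log-SD 0.5 and CV 20–30%, patients with TG <200 would show a spurious median rise of about 4.8 to 10.8%.

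**Cost.** A few extra tables, one recorded item and some wording; no extra blood tests. The corrected figures may over-correct, because Week 24–48 variance also contains true change such as altered adherence, so they should be supportive only.

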#### Inclusion criteria

2.2.2

To be eligible for this study, participants must meet all of the following criteria.

Age ≥19 years old at the time of written informed consent.Participants diagnosed with dyslipidemia and metabolic syndrome as defined in Section 2.2.1.Participants who had no treatment history with lipid regulators within 4 weeks prior to Visit 1 or who had insufficient therapeutic effects from ≥8 weeks of treatment with lipid regulators using the same dosage and administration (these two subgroups—treatment-naïve and inadequate-response—will be pre-specified and analyzed separately as a key subgroup analysis, as they may exhibit differential LDL-C response).Participants who meet the following LDL-C levels according to the classification of cardiovascular disease risk groups (9) (**Table 2**) at Visit 1 or who are planned to be treated with LivaloZet^®^ Tablets based on the judgment of the investigator.Participants who voluntarily sign the informed consent form for study participation.

**Table 2 T2:** Classification of cardiovascular risk groups and target LDL-C level.

Risk group	Criteria for classification	LDL-C (mg/dL)
Very high risk group	Coronary artery disease	≥ 55
High risk group	Atherosclerotic ischemic stroke, transient ischemic attack, carotid artery disease, peripheral arterial disease, abdominal aortic aneurysm, diabetes mellitus (duration of disease ≥10 years; or concurrent major cardiovascular disease risk factors† or target organ damage‡)	≥ 70
Diabetes group	Diabetes mellitus (duration of disease <10 years, no major cardiovascular disease risk factors†)	≥ 100
Moderate risk group	≥2 major cardiovascular disease risk factors†	≥ 130
Low risk group	≤1 major cardiovascular disease risk factor†	≥ 160

† Major cardiovascular disease risk factors (1): Age: ≥ 45 years old in men, ≥ 55 years old in women; (2) Family history of early onset coronary artery disease: Parents or siblings who had an onset of coronary artery disease at the age of <55 years in men and <65 years in women; (3) Hypertension: Systolic blood pressure (SBP) ≥ 140 mmHg or diastolic blood pressure (DBP) ≥ 90 mmHg or treatment with antihypertensives; (4) Current smoking; (5) High density lipoprotein-cholesterol (HDL-C) < 40 mg/dL (If HDL-C ≥ 60 mg/dL, 1 will be subtracted from the number of major risk factors).

‡ Target organ damage: Albuminuria (including microalbuminuria), chronic kidney disease (estimated glomerular filtration rate [eGFR] < 60 mL/min/1.73 m²), retinopathy, neuropathy, left ventricular hypertrophy.

LDL-C, low-density lipoprotein cholesterol.

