**Methods and analysis:**

The PIVOT study is a multi-center, non-interventional, prospective observational study enrolling up to 10,000 Korean adult patients with dyslipidemia accompanied by metabolic syndrome who have been prescribed LivaloZet^®^ Tablets (pitavastatin/ezetimibe 2/10 mg or 4/10 mg) by their treating physician as part of routine clinical care. Metabolic syndrome is defined according to the modified NCEP-ATP III criteria for the Asian population. Assessments are conducted at baseline, Week 24, and Week 48. The primary endpoint is the percent change in low-density lipoprotein cholesterol (LDL-C) from baseline at Week 24. Secondary endpoints include LDL-C changes at Week 48, changes in the full lipid panel, and LDL-C target achievement rates by cardiovascular risk group. Exploratory endpoints encompass glucose metabolism parameters (HbA1c, HOMA-IR, HOMA-β), medication adherence and persistence, and high-sensitivity C-reactive protein. Safety is assessed through adverse events, laboratory tests, and vital signs, including systematic monitoring of AST, ALT, and creatine kinase for statin-related hepatotoxicity and myopathy. The study was approved by the Institutional Review Board of Chungnam National University Hospital (2025-07-065) and is registered at ClinicalTrials.gov (NCT07523971).

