### Cardiovascular risk classification

2.3

Cardiovascular risk classification (**Table 2**) is assigned by the treating investigator at Visit 1 (baseline), based on the patient’s clinical history, comorbidities, and available risk-factor data, in accordance with the 2022 KSoLA guidelines (9). If risk-factor data are incomplete for any participant, the investigator will assign the most conservative (higher-risk) category supported by available evidence, and the participant will be flagged for sensitivity analysis. Risk classification will not be re-assigned during follow-up; the baseline category determines target LDL-C used for goal-attainment analyses.

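### The LDL-C limb of inclusion criterion 4 excludes nobody, so the target achievement rate can mix reaching target with staying at target

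*Protocol article*

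**What the plan says.** Section 2.2.2 requires that "participants must meet all of the following criteria". Criterion 4 has two limbs. A participant has the LDL-C level that Table 2 gives for the risk group "at Visit 1 or who are planned to be treated with" the product in the investigator's judgment. The Abstract describes the study population as patients "who have been prescribed LivaloZet".

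Table 2 gives entry values of ≥55, ≥70, ≥100, ≥130 and ≥160 mg/dL for the very high risk, high risk, diabetes, moderate risk and low risk groups. Section 2.4.2 lists as a secondary endpoint the "Achievement rate (%) for target LDL-C level at Week 24 and Week 48", with targets of <55, <70, <100, <130 and <160 mg/dL for the same groups. Section 2.3 adds that "the baseline category determines target LDL-C used for goal-attainment analyses".

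The other entry rules that bear on LDL-C are these:
- Dyslipidemia (Section 2.2.1) is any one of "LDL-C ≥160 mg/dL, TC ≥240 mg/dL, HDL-C <40 mg/dL, or TG ≥200 mg/dL".
- Criterion 3 asks for no lipid regulator within 4 weeks or for "insufficient therapeutic effects from ≥8 weeks of treatment with lipid regulators" at a stable dosage. It attaches no LDL-C value to either.
- The exclusion criteria (Section 2.2.3) contain no LDL-C rule.

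**The concern.** An entry threshold joined by an or to a condition that everyone meets has no effect. Here the threshold is also the boundary of a secondary endpoint. A participant admitted below the Table 2 value is, by definition, at target on the first day. Followed as written, the endpoint counts that person as an achiever if the follow-up LDL-C is still below the target.

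The achievement rate would then combine two different quantities: how often people above target reach it, and how often people already at target remain there. The mix depends on who is enrolled, and it can vary between risk groups and centres. The Discussion gives attainment by risk group particular clinical importance, so readers are likely to compare these rates across groups and with other Korean data.

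**Working it through.** **Step 1. Does the LDL-C limb exclude anyone?** Criterion 4 is met if either limb is met. The second limb is being planned for treatment with the product, and the Abstract says all participants have been prescribed it. The second limb is therefore met by all, whatever their LDL-C.

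**Step 2. Does another rule set an LDL-C floor?** Dyslipidemia can be met on HDL-C, TG or TC alone. Criterion 3 sets no LDL-C condition for untreated participants and leaves insufficient effect undefined for pretreated ones. No exclusion concerns LDL-C. So there is no floor, although criterion 3 may filter some pretreated participants.

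**Step 3. An admissible case.** Take an untreated, non-smoking, normotensive man aged 40 with normal glucose and no relevant family history. His waist is 92 cm, TG 210, HDL-C 38 and LDL-C 120 mg/dL.
- Dyslipidemia: yes, on TG ≥200 and on HDL-C <40.
- Metabolic syndrome: yes, three components (waist ≥90 cm, TG ≥150, HDL-C <40).
- Risk group: low, with one major risk factor (HDL-C <40; age is below 45).
- Target: <160 mg/dL. He enters 160 − 120 = 40 mg/dL below it.

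In the low risk group, the LDL-C limb of the dyslipidemia definition (≥160) equals the Table 2 value, so anyone who qualifies only on TG, HDL-C or TC is at target at baseline. In the very high risk group this would need an LDL-C below 55. The scope for at-target entry therefore differs by risk group.

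**Step 4. Does the analysis separate these participants?** The full analysis set (Section 2.6.1) needs one dose and one post-baseline assessment, with no LDL-C condition. The only split by baseline LDL-C (Section 2.6.3) is at 130 mg/dL and is for the primary endpoint. It does not match the five group-specific boundaries.

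**Step 5. The plan's own precision figure.** The plan gives no figure for the achievement rate. Its stated precision is for the primary endpoint (Section 2.5: SD 22%, 8,000 analysed): 1.96 × 22/√8000 = 0.48, which agrees with about ±0.5%. This point does not affect it.

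**Step 6. Possible size.** Let *b* be the share at target at baseline, *a* the achievement rate among those above target, and *r* the share of at-target entrants still at target at follow-up. None is given in the document; all are assumptions.

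Rate as written = (1 − *b*)·*a* + *b*·*r*, so the difference from *a* is *b*·(*r* − *a*).

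With *a* = 60% and *r* = 90%, the difference is 30 × *b* points:

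| *b* | Rate as written | Difference (points) |
|---|---|---|
| 1% | 60.3% | 0.3 |
| 3% | 60.9% | 0.9 |
| 10% | 63% | 3 |
| 20% | 66% | 6 |
| 30% | 69% | 9 |

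With *r* = 95% and *b* from 5% to 30%, the difference is 2.25 to 13.5 points for *a* = 50%, 1.75 to 10.5 for *a* = 60%, and 1.25 to 7.5 for *a* = 70%.

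The sampling half-width of a pooled 60% rate with 8,000 analysed is 1.96 × √(0.6 × 0.4/8000) = 1.07 points. With *a* = 60% and *r* = 90%, the difference exceeds this once *b* is above 1.07/30 = 3.6%. Rates within a risk group have wider intervals.

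**Step 7. Comparison between groups.** If two risk groups had the same *a* = 60% and *r* = 90% but shares of 1% and 30%, their reported rates would be 60.3% and 69%. That is 8.7 points apart with no difference in response.

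**The case against.** The strongest reply is that nothing here need be an error. In a non-interventional study of routine use, entry on the physician's judgment can be deliberate. The proportion of treated patients below target at Week 24 or 48 is a legitimate descriptive quantity, and the study disclaims causal and comparative conclusions. Denominators for a secondary responder rate are often left to the analysis plan, which is not shown.

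Much of this stands. The all-FAS rate is not wrong in itself, and an analysis plan could add a split by baseline status. What remains does not depend on an omitted detail: a stated threshold has no effect, and the stated endpoint, applied to the stated analysis set, takes no account of baseline status.

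A reader might infer more, namely that at-target participants will enter in numbers and that the rate is inflated by 3 to 9 points. The document does not support that:
- It permits such entry but does not show how common it will be.
- Pretreated participants must have had an insufficient effect, which filters some of them even though it is undefined.
- Prescribing follows the approved label (Section 2.1), and the Introduction describes the product as meant for patients who need potent LDL-C reduction or cannot take high-dose statin.
- An at-target entrant counts as an achiever only if still below target at follow-up.
- At a baseline share of 1% to 3%, the illustrative difference is only 0.3 to 0.9 points, below the pooled sampling error.

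**Conclusion.** The point holds in a limited form. The LDL-C limb of criterion 4 excludes nobody, and its values are the complements of the achievement targets. The plan thus allows participants already at target to be counted as achievers, mainly untreated participants who qualify on TG, HDL-C or TC, and most easily in the low risk group. The resulting rate mixes reaching target with maintaining it, to a degree that can differ by risk group.

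The logic follows from the text. The size does not: about 0.3 to 9 points for baseline shares of 1% to 30% rests wholly on the assumed 60% achievement and 90% maintenance. It should be read as a range of possibilities, not as an estimate of bias. The definition of the primary endpoint is not affected.

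**What to change.** 1. Report, by risk group, the share of participants whose baseline LDL-C is already below their target.
2. Make the main achievement rate the one among participants whose baseline LDL-C is at or above the Table 2 value for their risk group.
3. Report maintenance of target separately for those below that value at baseline, and give the all-FAS rate as supplementary.
4. Reconcile criterion 4 with Table 2 so that it is clear whether the LDL-C limb is meant to bind. Which way to settle this is for the sponsor and the investigators.

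Items 1 to 3 change the analysis only. Table 1 already requires LDL-C and risk classification at Visit 1, so no new data are needed. The cost is a smaller denominator for the main rate, hence somewhat wider intervals, and possibly a lower reported rate.
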